## Abstract

**Background:**

Stereotactic ablative radiotherapy (SABR) has emerged as a new treatment option for patients with oligometastatic disease. SABR delivers precise, high-dose, hypofractionated radiotherapy, and achieves excellent rates of local control. Survival outcomes for patients with oligometastatic disease treated with SABR appear promising, but conclusions are limited by patient selection, and the lack of adequate controls in most studies. The goal of this multicenter randomized phase II trial is to assess the impact of a comprehensive oligometastatic SABR treatment program on overall survival and quality of life in patients with up to 5 metastatic cancer lesions, compared to patients who receive standard of care treatment alone.

**Methods:**

After stratification by the number of metastases (1-3 vs. 4-5), patients will be randomized between Arm 1: current standard of care treatment, and Arm 2: standard of care treatment + SABR to all sites of known disease. Patients will be randomized in a 1:2 ratio to Arm 1:Arm 2, respectively. For patients receiving SABR, radiotherapy dose and fractionation depends on the site of metastasis and the proximity to critical normal structures. This study aims to accrue a total of 99 patients within four years. The primary endpoint is overall survival, and secondary endpoints include quality of life, toxicity, progression-free survival, lesion control rate, and number of cycles of further chemotherapy/systemic therapy.

**Discussion:**

This study will provide an assessment of the impact of SABR on clinical outcomes and quality of life, to determine if long-term survival can be achieved for selected patients with oligometastatic disease, and will inform the design of a possible phase III study.

**Trial registration:**

Clinicaltrials.gov identifier: NCT01446744

## Background

The oligometastatic disease state was first defined in 1995 and refers to an stage of disease where cancer has spread beyond the site of origin, but is not yet widely metastatic [1]. In such a state of limited metastatic disease burden, it is hypothesized that eradication of all sites of metastatic disease could result in long-term survival, or even cure, in a subgroup of patients [2]. Ablation of metastatic deposits can be achieved surgically, or through stereotactic ablative radiotherapy (SABR), a new radiotherapy technology that delivers very large, hypofractionated doses of radiotherapy with high precision to small tumor targets, with high rates of local control.

Clinical evidence to support the presence of an oligometastatic state is emerging in both the surgical and SABR literature, for several tumor types. In a study of over 5200 patients with lung metastases who underwent surgical resection, a 5-year survival of 36% was reported in patients who achieved a complete resection, much higher than would be expected for many patients with disseminated stage IV disease [3]. Similarly, in patients treated with SABR for 1-3 lung metastases from a variety of primary tumors, local control with SABR was 96% at 2-years, and 2-year survival was 39% [4]. Long-term survival has been demonstrated in patients treated for oligometastases with surgery or SABR at several other tumor sites, including liver, brain, bone, and adrenal metastases [2,5-8]. However, even after such treatment, the risk of further metastases after ablative treatment is high, up to 60-80% in some studies [4,5]. In some cases, SABR can be used for further salvage at newly progressive sites [9].

Despite the apparent achievement of long-term survival with ablative treatment for oligometastatic disease, the level of evidence to support such treatments is weak in many cases, often based on single-arm studies without appropriate controls [10]. Patients included in such reports are highly selected, based on good performance status and slow pace of tumor progression. It has been suggested that the long-term survival achieved with treatment of oligometastases is a result of the selection of fit patients with very slow-growing tumors, rather than the result of treatment intervention [11].

Randomized trials are therefore necessary to establish the utility of ablative treatment of oligometastatic disease [10,12], but such randomized trials are rare. One such completed randomized trial, Radiation Therapy and Oncology Group Trial 9508, compared whole brain radiotherapy (WBRT) with WBRT + stereotactic treatment for patients with 1-3 brain metastases, and found an overall survival advantage only in patients with a single metastasis and those patients in the most favorable baseline recursive partitioning analysis (RPA) prognostic group [13]. Patients with inferior baseline prognostic factors did not achieve a survival benefit from stereotactic treatment. At least one other randomized trial investigating the oligometastatic paradigm has recently opened: in 2010, the Pulmonary Metastasectomy in Colorectal Cancer (PulMiCC) trial was launched, comparing metastatectomy with best supportive care in patients with pulmonary metastases from colorectal cancer [14].

It is unclear if all patients with oligometastatic disease benefit from SABR, in terms of improved local control, improved survival or improved quality of life. Although SABR generally results in ablation of each metastatic target, patients remain at high risk of further metastatic progression. Results from SABR for treatment of oligometastases in published studies appears promising, but these promising results may be due to patient selection, rather than treatment intervention, and are based on comparisons with historical controls. The benefit of comprehensive treatment of oligometastases can only be demonstrated conclusively in the context of a randomized trial.

## Methods/design

This study is designed as a randomized phase II study. Patients will be randomized between current standard of care treatment (Arm 1) vs. standard of care treatment + SABR (Arm 2) to sites of known disease (Figure 1). Patients will be randomized in a 1:2 ratio to Arm 1 vs. Arm 2, respectively. This study has been approved by the Ontario Cancer Research Ethics Board (#11-030), in compliance with the Helsinki Declaration.

**Figure 1 F1:**
[figure not shown]
** Study design.** Patients with be randomized in a 1:2 ratio between Arm 1 (Standard of care) vs. Arm 2 (SABR).

The randomized phase II design is required for 3 reasons: First, the randomization will provide an appropriate control group to serve as a comparator for the experimental arm. Historical or contemporaneous non-randomized controls would not be appropriate due to the multitude of biases that could be introduced by patient selection and other confounders. Second, a small sample size will allow for adequate power to assess for an early overall survival difference, quality of life, and to evaluate toxicity in the SABR arm. Third, the results will allow for a decision as to whether a multi-institutional phase III trial is warranted, and inform the design of such a trial.

### Objectives

To assess the impact of a comprehensive oligometastatic SABR treatment program on overall survival and quality of life in patients with up to 5 metastatic cancer lesions, compared to patients who receive standard of care treatment alone.

#### Primary endpoint

· Overall Survival

· Defined as time from randomization to death from any cause

#### Secondary endpoints

· Quality of life

· Assessed with the Functional Assessment of Cancer Therapy: General (FACT-G)

· Toxicity

· Assessed by the National Cancer Institute Common Toxicity Criteria (NCI-CTC) version 4 for each organ treated (e.g. liver, lung, bone)]

· Progression-free survival

· Time from randomization to disease progression at any site or death

· Lesional control rate

· Number of cycles of further chemotherapy/systemic therapy

### Inclusion criteria

· Age 18 or older

· Willing to provide informed consent

· Histologically confirmed malignancy with metastatic disease detected on imaging. Biopsy of metastasis is preferred, but not required.

· ECOG performance status 0-1

· Controlled primary tumor

· defined as: at least 3 months since original tumor treated definitively, with no progression at primary site

· All sites of disease can be safely treated based on criteria below

· Maximum 3 metastases in any single organ system (i.e. lung, liver, brain, bone), and the total number of metastases must be 5 or less. For example, a patient with two liver metastases and two lung metastases is eligible.

· Life expectancy >6 months

· Not a candidate for surgical resection at all sites: surgery to all sites not recommended by multidisciplinary team, or unfit or declining surgery

· Prior chemotherapy allowed but no chemotherapy (cytotoxic or molecularly targeted agents) therapy 4 weeks prior to first fraction of radiotherapy, during radiotherapy, or for two weeks after last fraction. Hormonal therapy is allowed.

· Patients with metastases that have been previously treated (e.g. prior resection, RFA or radiotherapy):

· If that previously treated metastasis is controlled on imaging, the patient is eligible for this study and that site does not need treatment

· If that previously treated metastasis is NOT controlled on imaging:

· If the previous treatment was surgery, the patient is eligible if that site can be treated by SABR

· If the previous treatment was radiotherapy or RFA, the patient is ineligibile.

· Patient presented at multidisciplinary tumor board or radiotherapy departmental quality-assurance rounds, with consensus opinion that entry into the study is appropriate.

### Exclusion criteria

· Serious medical comorbidities precluding radiotherapy

· Bone metastasis in a femoral bone

· Patients with 1-3 brain metastasis and no disease elsewhere (these patients should not be randomized but treated with stereotactic radiotherapy as per results of randomized trials)

· Prior radiotherapy to a site requiring treatment

· Complete response to first-line chemotherapy (i.e. no measurable target for SABR)

· Malignant pleural effusion

· Inability to treat all sites of active disease

· Clinical or radiologic evidence of spinal cord compression OR tumor within 3 mm of spinal cord on MRI.

· Dominant brain metastasis requiring surgical decompression

· Pregnant or lactating women

### Evaluation and randomization

Prior to randomization, a complete history and physical examination by the treating radiation oncologist is required. Histologically confirmation of malignancy is required, with metastatic disease detected on imaging. Biopsy of metastasis is preferred, but not required.

Patients must be restaged within 12 weeks prior to randomization, including brain CT or MRI imaging (for tumor sites with propensity for brain metastasis); and CT neck/chest/abdomen/pelvis with bone scan. PET-CT is only required for specific evidence-based indications, as defined by the Ontario Health Insurance Program, and in such cases the CT neck/chest/abdomen/pelvis and bone scan are not required. For other indications, at the discretion of the treating oncologists, PET-CT scans may be done but are not required. MRI spine is required for patients with vertebral or paraspinal metastases.

Patients with liver metastases are also required to have adequate liver function tests (AST, ALT, GGT, alkaline phosphatase). A negative pregnancy test is required for women of child-bearing age.

The study will employ a 1:2 randomization between Arm 1:Arm 2 (Figure 1). The sample size allows for one stratification factor at randomization: number of metastatic sites (1-3 vs. 4-5). Randomization will occur in permuted blocks of nine.

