#### Primary endpoint

Survival will be calculated using the Kaplan-Meier method with differences compared using the stratified log-rank test. Pre-planned subgroup analysis will occur based on stratification variables. A Cox multivariable regression analysis will be used to determine baseline factors predictive of survival and allow for assessment of time to failure data important in this patient group.

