## Discussion

Although the aggressive treatment of patients with oligometastatic disease has become more common over the last decade [24], considerable equipoise still exists as to whether such aggressive treatments improve overall survival, or whether the long-term survival seen in single-arm studies is due to patient selection and treatment of slow-growing, favorable tumors [25]. Although SABR and surgical resection of oligometastases are generally safe, there is a risk of toxicity, and a small risk of treatment-related mortality [26,27]. Since patients with metastatic disease have traditionally been considered to be best served by palliative treatments, it is incumbent upon physicians to demonstrate that the escalation of treatment (with attendant risks of side effects or complications) is associated with gains in survival and/or quality of life.

This multicenter, international study aims to accrue 99 patients and aims to provide preliminary evidence to assess the impact of a comprehensive oligometastatic SABR treatment program on overall survival and quality of life. Data from this study may be used to inform the design of a phase III study, and will lead to a better understanding of the oligometastatic paradigm.

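### All primary tumour types are eligible, but the primary survival comparison takes no account of tumour type: valid in size, but open to lost power and an uncorrected chance imbalance

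*Protocol article*

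**What the plan says.** Under Inclusion criteria, the protocol article requires only "Histologically confirmed malignancy with metastatic disease detected on imaging"; primary site is not restricted. Under Evaluation and randomization it states: "The sample size allows for one stratification factor at randomization: number of metastatic sites (1-3 vs. 4-5"), and adds: "Randomization will occur in permuted blocks of nine".

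Under Data analysis, Primary endpoint: "Survival will be calculated using the Kaplan-Meier method with differences compared using the stratified log-rank test". The article defines no stratification factor other than number of metastases. The same paragraph continues: "A Cox multivariable regression analysis will be used to determine baseline factors predictive of survival". It names no covariates for that model and does not say that the model yields an adjusted treatment effect.

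The Background reports the suggestion that long survival after ablation is "a result of the selection of fit patients with very slow-growing tumors, rather than the result of treatment intervention", and the Discussion repeats that survival in single-arm studies may be "due to patient selection and treatment of slow-growing, favorable tumors".

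**The concern.** Survival with metastatic disease may differ widely by primary tumour, and the article itself treats tumour pace as a rival explanation for good outcomes. Any primary is admitted and the control arm has 33 patients, so the mix of tumour types in the two arms can differ appreciably by chance. The test that decides the primary result makes no allowance for this.

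Two things are at stake. First, a strong prognostic factor left out of a survival analysis lowers power, which is scarce with about 80 expected deaths. Second, if the trial that is run happens to have more favourable tumours in one arm, nothing in the stated primary comparison corrects the result on which a phase III decision is to rest.

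The reason given for using one factor, the sample size, concerns strata at randomization. It does not limit what the analysis may adjust for.

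**Working it through.** **1. The plan's own sample size.** Inputs from Sample size: medians 9 and 15 months (hazard ratio 9/15 = 0.60 under exponential survival), 1:2 allocation, alpha 0.20, power 0.80, 48 months' accrual plus 12 months' follow-up. The article does not state sidedness.

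- Probability of death by the end of the study: 0.895 (control), 0.769 (SABR).
- Two-sided Schoenfeld: (1.282 + 0.842)² / [(1/3)(2/3)(ln 0.60)²] ≈ 78 deaths. The weighted death probability is (0.895 + 2 × 0.769)/3 = 0.811, so N = 78/0.811 ≈ 96.
- Log-hazard formula: 3 × (2.123²/0.261) × [1/0.895 + 1/(2 × 0.769)] ≈ 92. Lachin-Foulkes: about 95.
- One-sided, the same methods give only 58 to 61.

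The stated 93 therefore reproduces at two-sided 0.20. With 99 patients about 33 × 0.895 + 66 × 0.769 ≈ 80 deaths are expected, and power is 0.81. There is no arithmetic error here.

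**2. Chance imbalance.** For a favourable tumour group with prevalence p, the between-arm difference has SD √[p(1−p)(1/33 + 1/66)].

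| p | SD | P(differ by more than 10 points) | more than 15 | more than 20 |
|---|---|---|---|---|
| 20% | 0.085 | 24% | 8% | 2% |
| 30% | 0.098 | 31% | 13% | 4% |
| 50% | 0.107 | 35% | 16% | 6% |

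At p = 40% the SD is 0.104, and about 8% of trials have 15 points or more in SABR's favour. The opposite tail is equally likely. With no treatment effect, a 20-point imbalance moves the unadjusted hazard ratio to roughly exp(0.20 × ln 0.5) = 0.87 if favourable types have half the hazard, or exp(0.20 × ln 0.33) = 0.80 if they have a third.

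**3. Power.** The article gives neither the prevalence nor the prognostic strength of tumour type, so both are assumed. Set-up: 99 patients in blocks of 3:6, exponential survival within tumour group, control-arm median 9 months over the mix, treatment hazard ratio 0.60 within group, one-sided 0.10 (the upper half of two-sided 0.20), 3000 to 4000 simulated trials per scenario. Number of metastases was not modelled, since its distribution is not given. Because treatment multiplies every hazard by 0.60, the SABR survival curve at time t equals the control curve at 0.60t. The SABR median is therefore 9/0.60 = 15 months, so the plan's own medians are kept.

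Prevalence is 40%, except that the first two rows include runs at 20-40%. Ranges span repeated runs:

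| Prognostic HR (unfavourable vs favourable) | Power ignoring type | Power accounting for type |
|---|---|---|
| 1.5 | 78-82% | 79-81% |
| 2 | 77-79% | 80-81% |
| 3 | 70-71% | 78-81% |
| 4 | 64-66% | 78-80% |

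If type is not prognostic, stratifying by it costs about 1 point.

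**4. Type I error.** Two-sided error at nominal 0.20 is 0.20-0.21 whether or not type is used. In the roughly 8% of null trials with 15 points or more in SABR's favour, SABR is wrongly declared better in 21-38% ignoring type and in 9-14% accounting for it (nominal 10%, prognostic HR 2 to 4). That subset holds about 0.08 × 3000 = 240 trials, so its Monte Carlo standard error is near √(0.3 × 0.7/240) = 3 points.

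**The case against.** A reader might infer that tumour type confounds this trial, or that the plan leaves it unbalanced. The documents do not support that. Randomization balances tumour type in expectation, and chance imbalance is already counted in the test's error rate, which step 4 confirms. The remarks on slow-growing tumours in the Background and Discussion are aimed at uncontrolled studies, and Methods/design gives the randomized control group as the remedy. The article nowhere names histology as a threat to its own comparison. All of this stands.

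The article is also condensed, and the list of Cox covariates may sit in a document not shown. The missing list is therefore no defect in itself. What the article does fix is the deciding test and the stated purpose of the Cox model, and those are the subject of this point.

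The size of the loss rests on assumed inputs. It is small at a prognostic hazard ratio of 2 and negligible at 1.5. It also presumes an accurate grouping: with 20% of patients misgrouped, the gain at a hazard ratio of 3 shrinks from 70% → 78% to 70% → 73%, and at 2 to about 1 point. Eligibility (ECOG 0-1, controlled primary, at most five metastases) narrows prognosis somewhat. The false-positive rates in step 4 describe one chosen tail; the other tail works against SABR.

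Finally, one may infer that a second randomization factor is needed. It is not. Four strata would share 99/9 = 11 blocks, and the strata with 4-5 metastases could be too small to fill theirs. The trial also calls itself preliminary, which tempers the consequence but does not remove the benefit of a more precise analysis.

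**Conclusion.** The point holds as a matter of efficiency and robustness, not of validity. The stated primary test keeps its error rate and the sample size reproduces. But the test ignores a baseline characteristic that must be known at entry and that may be strongly prognostic in a trial open to every primary. Assuming 40% favourable types correctly grouped, accounting for type gains about 2 to 4 points of power at a prognostic hazard ratio of 2, 8 to 11 points at 3 and about 14 points at 4, with little or no gain at 1.5 or below. It also protects the reading of the one realized trial against a chance imbalance, which with 33 controls is quite plausible. The change should be made, because the cost is slight and the possible loss is not.

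**What to change.** Prespecify a Cox model for the treatment effect on overall survival, stratified by number of metastases (1-3 vs 4-5) and including a broad tumour-type group. Give it one of two stated roles: the primary estimate and test at the same 0.20 level, with the stratified log-rank test as supportive; or the named key adjusted analysis reported beside that test. Keep it separate from the exploratory search for predictive factors.

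Define the groups before any survival data by arm are reviewed, and so before the interim analysis at 50 patients. Keep them few, given about 80 expected deaths.

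Costs: a change of analysis wording and agreement on the groups. Histology is already required at entry, so no new data are needed. The hazard ratio becomes conditional on tumour group and should be labelled so; Kaplan-Meier medians can still be reported by arm. About 1 point of power is lost if type proves not to be prognostic. In simulation the adjusted Cox test had one-sided size 0.106-0.115 against 0.10, compared with 0.106-0.111 for the unadjusted log-rank test, so any further inflation is slight. A tumour-type factor at randomization may be added but is not required.

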## Interventions

### Arm 1

Radiotherapy for patients in the standard arm should follow the principles of palliative radiotherapy as per the individual institution, with the goal of alleviating symptoms or preventing imminent complications. Patients in this arm should not receive stereotactic doses or radiotherapy boosts.

Treatment recommendations for patients in Arm 1 are as follows: For brain metastases, whole brain radiotherapy (i.e. 20 Gy in 5 fractions, 30 Gy in 10 fractions); for lung metastases, palliative radiotherapy as per 2011 consensus guidelines (i.e. 8 Gy in 1 fraction, 20 Gy in 5 fractions, 30 Gy in 10 fractions)[15]; for bone metastases, palliative radiotherapy as per 2011 consensus guidelines (i.e. 8 Gy in 1 fraction (most common), 20 Gy in 5 fractions, 30 Gy in 10 fractions)[16]; for liver metastases, 20 Gy in 5 fractions if standard institutional practice.

For Arm 1, Treatment planning is to be done using CT simulation or conventional simulation (fluoroscopy) as per individual institutional practice. Simple beam arrangements, such as parallel opposed beams, are favored wherever possible.

### Arm 2

For Arm 2, all treatments in this study are based on current protocols in clinical use at the LRCP and VUmc for treatment of lung [17], liver [18], brain [19,20], and spinal column [21] metastases. The guiding principle for radiotherapy is to achieve disease control but to minimize any potential adverse impact on quality of life. Concurrent chemotherapy or targeted therapy at the time of radiotherapy is not permitted within the 4 weeks prior to SABR. Hormone therapy is permitted.

Doses and fractionations by tumor site are shown in Table 1. Treatment will be setup using reproducible positioning, verified using an on-line protocol, for all patients in this study. Immobilization may include a custom immobilization device, such as thermoplastic shell or Vac-lok^TM^ bag, as per individual institutional practice when delivering SABR. Some centers do not use immobilization devices and have demonstrated high degrees of accuracy; this is acceptable in this study.

**Table 1 T1:** Dose and fractionations by site

**Tumor Location**	**Description**	**Total Dose (Gy)**	**Number of fractions**	**Dose per fraction (Gy)**	**Frequency**
**Lung**	Tumors 3 cm or less surrounded by lung parenchyma	54	3	18	Every second day
	Abutting chest wall or >3 cm	55	5	11	Every second day
	Within 2 cm of mediastinum or brachial plexus	60	8*	7.5	Every second day

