## Statistical analysis

### Sample size

This study will employ a randomized phase II design, to conduct a preliminary and non-definitive randomized comparison between the control and experimental arms. The study will aim to detect a signal in improved overall survival that would be used to design a phase III study to definitely compare survival outcomes between the two groups. The study will therefore be designed with alpha = 0.20 and beta = 0.20 (as recommended for phase II randomized studies [23]). It is estimated that the median survival of the control group after randomization in this study will be 9 months.

There will be a 1:2 randomization between Arm 1 and Arm 2. In order to detect a 6-month improvement in median survival from 9 months to 15 months with SABR, a total of 93 patients (31 in Arm 1 and 62 in Arm 2) will be needed. Assuming a 5% rate of loss to follow-up, a total of 99 patients will be accrued (33 in Arm 1 and 66 in Arm 2). The study projects accrual over 48 months with 12 months of additional follow-up. Accrual targets are as follows: 20 patients in year 1, and 25-30 patients in years 2, 3, and 4.

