### Data safety monitoring committee

The DSMC will meet annually after study initiation and after 50 patients are accrued to review toxicity outcomes. If any grade 3-5 toxicity is reported, the DSMC will review the case notes to determine if such toxicity is related to treatment. If the DSMC deems that toxicity rates are excessive (>25% grade 3 toxicity, or >5% grade 4 or 5 toxicity), then the DSMC can, at its discretion, recommend cessation of the trial, dose adjustment, or exclusion of certain treatment sites that are deemed as high-risk for complications.

The DSMC will conduct one interim analysis once 50 patients are accrued. For this analysis, the DSMC will be blinded to the identity of each treatment arm, but OS data will be presented for each arm. The DSMC will recommend stopping the trial if there is an OS difference that is statistically significant with a threshold of p < 0.001 using the log-rank test. Furthermore, if the median OS among all patients is substantially different than estimated in the sample size calculation, the DSMC can recommend increasing or decreasing the target accrual in order to maintain statistical power.

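### A single published block size of nine lets someone who sees a whole stratum foresee some allocations with certainty; undisclosed mixed block sizes would be a cheap improvement

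*Protocol article*

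**What the plan says.** Protocol article, Evaluation and randomization: allocation is 1:2 to Arm 1 and Arm 2, with one stratification factor at two levels (1-3 versus 4-5 metastatic sites). Then: "Randomization will occur in permuted blocks of nine". No other size is given, and nothing says that sizes vary or are withheld from sites. Centre is not a stratification factor, although the Discussion describes the trial so: "This multicenter, international study aims to accrue 99 patients".

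The article does not use the term open-label, but the arms are plainly distinguishable to those who treat. Of Arm 1, the Interventions section says: "Patients in this arm should not receive stereotactic doses or radiotherapy boosts". Arm 2 receives SABR. The only masking described is under Data safety monitoring committee, for the interim analysis: "For this analysis, the DSMC will be blinded to the identity of each treatment arm".

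Eligibility is mostly concrete, but the Inclusion criteria also ask for a life expectancy above 6 months and for presentation at a tumor board or quality-assurance rounds, "with consensus opinion that entry into the study is appropriate".

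**The concern.** With one known block length and visible treatment, the end of a block can be deduced. Once three Arm 1 patients in a block are known, the rest are Arm 2; once six Arm 2 patients are known, the rest are Arm 1. If the person who can deduce this also influences who is entered, or when, a prognostic difference between arms can arise before randomization.

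That would weaken the comparison where this trial most needs strength. The Background argues that promising results with ablative treatment may reflect patient selection, and gives this as the reason to randomize. Intention-to-treat analysis does not protect against selection before allocation. Nor does an objective endpoint such as death from any cause, because the bias would lie in who enters each arm. A motive is conceivable: Arm 1 patients are not to receive stereotactic doses, whereas Arm 2 patients are to be considered for SABR again at new sites.

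**Working it through.** The article gives no figure for predictability, so there is none to reproduce. Its planned numbers fit the block: 99 = 11 × 9, and 11 × 3 = 33 and 11 × 6 = 66.

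**Inputs from the Protocol article.** Block size 9; ratio 1:2, hence 3 Arm 1 and 6 Arm 2 per block; two strata; 99 patients.

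**Assumptions.** Blocks are built within strata. Each centre's share of accrual is not given, so a range is shown.

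**1. Observer who sees every allocation in a stratum.** There are C(9,3) = 84 equally likely orders. An allocation is certain when all r places still open in the block (this one included) go to one arm. The chance is C(9−r, 3)/84 for all Arm 2 and, for r ≤ 3, C(9−r, 3−r)/84 for all Arm 1.

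| Place in block | Certain Arm 2 | Certain Arm 1 | Certain, total |
|---|---|---|---|
| 1 to 3 | 0 | 0 | 0% |
| 4 | 1/84 | 0 | 1.2% |
| 5 | 4/84 | 0 | 4.8% |
| 6 | 10/84 | 0 | 11.9% |
| 7 | 20/84 | 1/84 | 25% |
| 8 | 35/84 | 7/84 | 50% |
| 9 | 56/84 | 28/84 | 100% |
| Sum | 126/84 = 1.50 | 36/84 = 0.43 | 162/84 = 1.93 |

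The closed form agrees: 6/(3+1) + 3/(6+1) = 1.50 + 0.43 = 1.93, and 1.93/9 = 21.4%. Over 11 complete blocks that is 11 × 1.93 ≈ 21 of 99 allocations, of which 11 × 0.43 ≈ 5 are Arm 1. Blocks left unfinished in either stratum would lower this a little.

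**2. Best guess rather than certainty.** Always guessing Arm 2 is right 6/9 = 66.7% of the time. Guessing the arm with more places left gives G(a,b) = max(a,b)/(a+b) + [a·G(a−1,b) + b·G(a,b−1)]/(a+b). Then G(3,6) = 6.55, and 6.55/9 = 72.8%.

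**3. Site that sees only its own patients.** Simulation of 60,000 blocks per scenario. Each patient belongs to the site with the assumed probability, and the site knows where blocks start but not the allocations elsewhere.

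| Assumed share of accrual | Own allocations known with certainty |
|---|---|
| 75% | about 8% |
| 50% | about 2% |
| 33% | about 0.6% |
| 25% | about 0.3% |

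**4. Other fixed sizes at 1:2.** Size 3: (1/3 + 2/2)/3 = 44%. Size 6: (2/5 + 4/3)/6 = 29%. Size 9: 21%.

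**5. Mixed sizes of 6, 9 and 12.** Simulation of about 100,000 allocations in sequences of 99. Sizes are drawn with equal probability, and the observer sees everything and knows the set of sizes but not their order. Certain allocations fall to about 2%; best-guess accuracy is 71.7%. The same program with fixed nine gives 21.7% and 72.8%, in line with the exact results above.

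**The case against.** The case for leaving the sentence alone has real weight.

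- **The 21% describes an unusual observer.** It requires sight of a whole stratum across centres. The article does not place such a person at the point of enrolment and gives no accrual share by centre. The site figures above are themselves generous, because a site that sees only its own patients would not normally know where blocks begin. This stands.
- **Most certain places say little.** Of the 1.93, 1.50 are Arm 2, the arm already expected two times in three. Only 0.43 of nine (4.8%) are certain Arm 1. This stands.
- **Nine is a fairly long block at 1:2**, better than three or six, and mixing sizes barely alters best-guess accuracy. This stands too. The gain lies in removing certain allocations, and almost wholly for the well-informed observer.
- **Entry is a group decision** at a tumor board or quality-assurance rounds, which limits what one recruiter can do. This stands in part: the consensus is still a judgement, and the timing of entry retains some latitude.
- **Concealment procedures may be in the full protocol.** That is fair, and their absence here is not held against the plan. The block size, however, is a stated rule and is now public.

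A reader might infer that recruiting investigators can foresee one allocation in five, or that the survival comparison is compromised. The documents support neither. The first confuses a site with an observer of the whole stratum. For the second, nothing indicates that any entry was steered, and the effect of steering a few patients has not been quantified.

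**Conclusion.** The point holds as a low-severity, inexpensive improvement to a stated design rule. It is not an error or a contradiction: the sample size, the stratified log-rank test and the endpoint definition are untouched. For an observer of a full stratum, 21% of allocations are certain in advance. For a site confined to its own patients, the share runs from about 8% down to a fraction of a percent as its share of accrual falls from 75% to 25%. The practical exposure is therefore a centre that both coordinates and recruits heavily, and the article does not say whether one exists. The conclusion rests on blocks being built within strata, on treatment being visible to staff (inferred from the interventions), and on the assumed accrual shares.

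**What to change.** For any blocks not yet used, replace the sentence on block size with one saying that permuted blocks of randomly varying size, each preserving 1:2, are used within strata, and that the sizes are known only to the randomization office. Sizes of 6, 9 and 12 would serve. The sizes should not appear in documents that sites receive. Publication of the nine cannot be undone, but it would no longer describe the remaining sequence.

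For the fully informed observer this cuts certain allocations from 21% to about 2%. Mixtures of 6 and 9, or of 3, 6 and 9, give about 5% and 4%.

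The cost is regenerating the unused part of the list and accepting a slightly larger possible departure from exact 1:2 at the end. Whether any of the list remains unused cannot be told from the article; if none does, there is nothing to change.
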